### Study design and setting

This is an 8-week, controlled, single-blind, three-arm, parallel, RCT, which will take place at the Faculty of Nutrition and Food Sciences and the Faculty of Sports of the University of Porto, at the Exercise Medical Center (CMEP) in Porto and at the Research Center in Sports Sciences, Health Sciences and Human Development (CIDESD) of the University of Maia. Participants will be randomly assigned into three independent groups (*n* = 16, in each) and the experimental design will consist of (a) pre-intervention tests, (b) familiarization period, (c) experimental intervention and (d) post-intervention tests.

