### Assignment of intervention

Participants confirmed as eligible will be randomized at a ratio of 1:1:1 to each group in blocks of four participants until complete the total number calculated (*n* = 48). A computer-generated random numerical sequence will be used for randomizing participants (Research Randomizer). The principal researcher will generate the sequence and conceal it in sealed, numbered opaque envelopes. Participants will be allocated a sequential number upon screening. The sealed envelope corresponding to the allocated participant number will be opened on the first visit by the principal researcher, and the participants will be allocated, without knowing which group they will belong to. As this is a single-blind study, blinding is not required for principal researcher, only to participants. A Consolidated Standards of Reporting Trials (CONSORT) flow chart outlining the study phases is displayed in Figure 2 (Moher et al., 2001).

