### Statistical considerations

For sample and power calculations, this study is powered based on changes in hemoglobin A1c in RCTs included in the meta-analysis by Zuuren et al. (2018), which tested the effect of carbohydrate restriction up to 8 weeks. Considering a type I error of 5% and a power of 80% to detect differences at the dependent variable with a statistical significance when comparing 3 independent groups (CTRL versus EH and EH versus EH + LCD), and an effect size of 1.14, a sample size of 14 participants per group will be needed, totaling 42 individuals. With an assumption of a 20% dropout rate, we will recruit 48 participants. The sample size calculations were performed using the Statistical Power Analyses for Windows, (G*Power 3.1.9.4, Uni Kiel, Germany).

Statistical analysis will be performed using SPSS statistics software version 28.0, 2021 (IBM Company, Chicago, United States). All data will be reported as mean ± SD and statistical significance will be assumed at *p* ≤ 0.05. Pairwise comparisons will be analyzed using the Wilcoxon test. A two-way repeated measures ANOVA will be used to examine changes in cardiopulmonary parameters, body composition, glycemic profile, and cardiovascular risk factors over the chronic exercise period (0 vs. 8 weeks), and whether the magnitude of the chronic exercise-mediated adaptations differ between groups (EH vs. CTRL; LCD + EH vs. EH). When a significant main- or interaction-effect will be found, Bonferroni post hoc tests for multiple pairwise comparisons will be performed to identify differences between groups.

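### Blocks of four cannot be balanced across three arms, so the stated block size contradicts the 1:1:1 ratio and does not guarantee 16 per arm

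*Protocol article*

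**What the plan says.** Under *Assignment of intervention*, the protocol article states that eligible participants will be "randomized at a ratio of 1:1:1 to each group in blocks of four participants" until 48 have been allocated. The sequence comes from a web-based randomizer and is held in sealed, numbered envelopes. The composition of a block is not described.

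Under *Study design and setting*, the article states: "Participants will be randomly assigned into three independent groups", with 16 in each.

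Under *Statistical considerations*, it takes a 5% type I error, 80% power and "an effect size of 1.14", and arrives at 14 per group. Recruitment is raised to 48 for dropout. The planned comparisons are EH against control, and EH plus low-carbohydrate diet against EH, so EH enters both.

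On numbering, *Assignment of intervention* also says: "Participants will be allocated a sequential number upon screening". The envelope that matches that number is opened at the first visit.

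**The concern.** A permuted block secures a ratio because every completed block holds the arms in that ratio. With three arms and four places, one arm must appear twice in each block. The article fixes both the ratio and the block size, and the two do not fit together. Whoever builds the list has to choose how to fill the fourth place, and that choice decides the final arm sizes.

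At stake are the equal arms on which the sample size rests, and the small reserve of two participants per arm above the 14 required. A short EH arm would affect both planned contrasts. The choice also falls to the principal researcher, who generates the sequence, opens the envelopes and is not blinded. That is a reason to write the rule down.

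**Working it through.** **Inputs.** Three arms, 1:1:1, blocks of four, total 48 (*Assignment of intervention*). Target 16 per arm (*Study design and setting*). Effect size 1.14, alpha 5%, power 80%, 14 per group (*Statistical considerations*). Sidedness is not stated, so two-sided is assumed.

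**The plan's own figures.**
- 48/3 = 16 per arm, as stated.
- Two-sample t test (noncentral t, n₁ + n₂ − 2 degrees of freedom, noncentrality 1.14/√(1/n₁ + 1/n₂)): power is 79.6% at 13 per group and 82.7% at 14. The stated 14 per group therefore reproduces.

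**Block arithmetic.** 48/4 = 12 complete blocks. 4/3 = 1.33 places per arm per block, which is not a whole number, so every block is 2-1-1 in some order. Each arm receives 12 places plus one for each block in which it is doubled. Arm sizes are 12 + a, 12 + b and 12 + c, with a + b + c = 12.

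**Arm sizes by rule for the fourth place.**

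| Rule | Result |
|---|---|
| Doubled arm rotated, four blocks each | 16/16/16 with certainty |
| Four read as four per arm (four blocks of 12) | 16/16/16 with certainty |
| Doubled arm drawn at random per block | P(16/16/16) = [12!/(4!)³]/3¹² = 34650/531441 = 6.5% |
| Extra place fixed on one arm | 24/12/12 |
| No effective blocking | P(16/16/16) = [48!/(16!)³]/3⁴⁸ = 1.7% |

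**Size of the EH arm under the random rule.** The number of blocks that double EH is binomial (12, 1/3).
- P(EH ≤ 14) = P(X ≤ 2) = 0.0077 + 0.0462 + 0.1272 = 18.1%.
- P(EH ≤ 13) = P(X ≤ 1) = 0.0077 + 0.0462 = 5.4%.
- That at least one of the three arms is this small has probability 51.8% (≤ 14) and 16.1% (≤ 13). These are not figures for EH.
- All three arms lie within 14 to 18 in 73% of sequences.

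**Power by arm sizes** (same t test, effect size 1.14, before dropout).

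| Contrast | Power |
|---|---|
| 16 v 16 | 87.7% |
| 14 v 18 | 87.2% |
| 13 v 17 | 84.8% |
| 12 v 24 | 87.9% |
| 12 v 12 | 76.1% |

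Averaged over all sequences of the random rule, a contrast of two arms has 87.3% power, a loss of 87.7 − 87.3 = 0.4 points. The 12 v 12 contrast arises under a fixed extra place. It is a planned contrast only if the doubled arm is control or EH plus diet, since a doubled EH arm makes both planned contrasts 12 v 24.

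**With a block size that fits.** Sizes 3, 6 and 12 are multiples of three and divide 48 (16, 8 and 4 complete blocks, no remainder). Each gives 16/16/16 with certainty.

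**The case against.** The strongest reply is that the inconsistency lies in one sentence and may do no harm. Forty-eight is divisible by both three and four, and a list of 2-1-1 blocks with the doubled arm rotated delivers exactly 16/16/16. Four may also have meant four per arm. A condensed article need not describe the list in full. Modest chance imbalance leaves randomisation valid and hardly moves power.

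Most of this stands. A reader might infer that a 1:1:1 allocation is impossible here, that 16/16/16 will almost never occur, or that the power calculation is lost. The document supports none of these. The probability of 16/16/16 runs from 1.7% to 100% according to a rule that is not given, and power falls below 80% in any material way only if the extra place is fixed on one arm. What does not stand is the appeal to condensation. The article states a block size, and that size conflicts with the ratio in the same sentence.

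A reader might also infer that each screen failure uses up an envelope and so breaks the blocks, because numbers are given at screening. That is one reading. The same section says that those randomised are already confirmed as eligible, the article does not say that numbers are lost, and no screen-failure rate is given. This is a point of wording to clarify, not an established defect.

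**Conclusion.** The stated block size contradicts the stated ratio and does not by itself deliver 16 per arm. This follows from arithmetic and needs no assumption. The consequence depends on the unstated rule for the fourth place: none under rotation; unequal arms with little loss of power under a random draw; and a 24/12/12 split under a fixed extra place, where the 12 v 12 contrast falls to about 76% before dropout.

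The power figures assume a two-sided 5% t test and the protocol's effect size of 1.14. No bias in the treatment effect is shown. Severity is minor to moderate: the sentence is wrong as written and should be corrected, but it does not threaten the validity of the comparison.

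**What to change.** Replace the blocks of four with permuted blocks whose size is a multiple of three. Randomly ordered 3s and 6s that fill 48 would do, for example eight blocks of 3 and four of 6 (24 + 24 = 48). State that the envelope number is assigned only after eligibility is confirmed.

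The article puts the end of recruitment at September 2023, so allocation may already have begun. In that case, report how the blocks of four were actually built and the arm sizes reached, and use the corrected blocks for the remainder. The corrected blocks will not remove an imbalance that already exists.

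The cost is a sentence or two in the protocol and a regenerated list, with no added participants or visits.

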### Interventions

Volunteers who meet the inclusion criteria will be asked to sign a written informed consent before enrolment in the trial, with the principal researcher. Participants will be randomized into control (CTRL), EH or interventions (EH + LCD) groups during 8 weeks. The CTRL group will perform an exercise protocol in normoxia with a control diet, and the other groups will perform the same exercise protocol in hypoxia (simulated altitude – nitrogen dilution method), following a control diet (EH) or an LCD (intervention group). Thus, we will compare whether EH group is more efficient than exercise in normoxia (CTRL group) and, if by including a LCD (EH + LCD group) the effects of EH group would be potentiated. We emphasize that during all test, physical exercise professionals, nutritionist, and doctors or nurses will be available.

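### The unblinded principal researcher makes the random list, prepares and opens the envelopes, and takes consent, so allocation is not concealed from the person enrolling

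*Protocol article*

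**What the plan says.** Assignment of intervention in the protocol article sets out the allocation chain. The sequence is computer-generated, and one person handles it: "The principal researcher will generate the sequence and conceal it in sealed, numbered opaque envelopes". On numbering it says: "Participants will be allocated a sequential number upon screening". On release it says: "The sealed envelope corresponding to the allocated participant number will be opened on the first visit by the principal researcher". On blinding it says: "As this is a single-blind study, blinding is not required for principal researcher, only to participants".

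The same section limits randomisation to those who pass screening: "Participants confirmed as eligible will be randomized at a ratio of 1:1:1 to each group in blocks of four participants", up to a total of 48.

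The Interventions section adds that volunteers who satisfy the inclusion criteria "will be asked to sign a written informed consent before enrolment in the trial, with the principal researcher".

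Data collection and management gives monitoring and auditing of the trial to the principal researcher together with the supervisory team.

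**The concern.** Allocation concealment means that whoever brings a participant into the trial cannot know the next assignment until entry is irrevocable. It is distinct from blinding after allocation and does not depend on it. A single-blind trial with open treatment staff can still be fully concealed at entry.

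Here one person writes the list and also enrols. Knowing the coming arm can affect how consent is discussed, whether a hesitant volunteer is encouraged, and whether someone is brought in this week or next. It could also affect eligibility calls that rest on judgement, if that person makes them. A laboratory outcome such as HbA1c gives no protection, because this bias acts on who enters each arm and not on how the outcome is read. With 16 participants planned per arm, a few such decisions could matter.

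A second, smaller issue lies in the same section. Numbers are given at screening and envelopes are matched to numbers, yet only eligible people are randomised. The text does not make clear which comes first, the number or the eligibility decision.

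**Working it through.** The plan states no figure on this point, so the check is a trace of roles and timing through the article.

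**Step 1: who holds each role.**

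| Step | Person named | Section |
|---|---|---|
| Generates the sequence | Principal researcher | Assignment of intervention |
| Prepares the envelopes | Principal researcher | Assignment of intervention |
| Takes consent before enrolment | Principal researcher | Interventions |
| Opens the envelope | Principal researcher, first visit | Assignment of intervention |
| Blinded to allocation | Participants only | Assignment of intervention |
| Issues the screening number | Not stated | – |
| Judges eligibility | Not stated | – |
| Monitors and audits | Principal researcher and supervisory team | Data collection and management |

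The case rests on the stated roles: making the list, preparing and opening the envelopes, and taking consent. It does not need the two that are not stated.

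**Step 2: what the envelopes conceal, and from whom.** Opaque sealed envelopes conceal from anyone who has not seen the list. Participants and other staff are in that position; the list's author is not. Envelope numbers follow participant numbers in sequence, so the author can read a participant's arm from the number alone. The author's chance of naming the next arm correctly is 1. Someone with no knowledge of the list or of past assignments, under 1:1:1 allocation, has a chance of 1/3.

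**Step 3: does the knowledge come early enough to act on?** Interventions puts the inclusion criteria first and consent second, and Assignment of intervention gives the number at screening. Taken in that order, the number, and with it the arm, can be known to the list's author before consent is signed. Even if numbers were issued later, the author would still know which arm the next entrant receives.

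**Step 4: is there discretion to influence?** Some entry criteria leave little: HbA1c from 6.5% to 10%, at least one year since diagnosis, three months on a stable regimen. Others need judgement: whether complications or comorbidities are uncontrolled, whether a person is sedentary, whether a physical limitation prevents exercise. The consent conversation and the timing of entry are discretionary whoever judges eligibility.

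**Step 5: the numbering, under both readings.**

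- *Number given once screening is passed:* every number belongs to an eligible person, and the list runs without gaps.
- *Number given when screening starts:* a person who fails screening holds a number whose envelope is never used, which leaves a gap in the list.

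The article does not settle which is meant.

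**The case against.** The strongest reply is that the article does specify a computer-generated sequence and sealed, numbered, opaque envelopes, which are recognised safeguards. That stands in part: a reader might infer that allocation is not concealed at all, and the text does not support this. Concealment holds for participants and other staff and fails for the person who enrols.

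A reader might also infer that the principal researcher controls eligibility. The article does not say so, and several criteria are fixed thresholds. That route is only possible; influence through consent and timing follows from the stated roles.

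It is tempting to conclude that every screen failure costs one of the 48 places. That depends on the second reading in the working. The opening of the section, which randomises only eligible people until 48 is reached, and the order given in Interventions both fit the first reading. The visit and flow figures are not available to settle it. What remains is an ambiguity to be resolved.

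It would also be too strong to say that no analysis could help. HbA1c is measured at baseline, so selection on it would be visible and could be adjusted for. Selection on traits that were not measured could not.

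Finally, predictability from small blocks adds nothing for someone who already holds the list.

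None of this removes the central point. It is an arrangement that the article states, not a detail left to a fuller protocol.

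**Conclusion.** The point holds in this form: allocation is concealed from participants and other staff, but not from the unblinded principal researcher, who takes consent. This permits selection bias at entry, through who is consented and when, and possibly through judgement-based eligibility calls. It does not show that such bias has occurred or will occur.

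No size in HbA1c points can be given. The documents do not say how many entries might be affected or how far those participants would differ from the rest, and any figure would be invented. The measurable part is the foreknowledge itself: certainty against 1 in 3.

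The conclusion assumes that the principal researcher keeps access to the list after making it, since no other holder is named, and that consent is taken by that person as written. The gap in the list from screen failures is conditional on numbers being issued before eligibility is known.

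The plan should be changed here. The threat is to the validity of a small randomised comparison, and removing it is cheap.

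**What to change.** 1. Have an existing team member with no role in consent, treatment or assessment generate and hold the list. The supervisory team is a natural place to look, but the article does not show that any of its members is free of those roles, so this must be confirmed.
2. Use block sizes that are not disclosed to the enrolling researcher. The published size of four cannot serve. New sizes should be multiples of three, because four does not divide evenly among three arms (a separate matter that the new list would also settle).
3. Issue the next number or envelope only after consent is signed, eligibility is confirmed and baseline tests are complete. Record the date and time before opening. Keep any screening identifier separate from the randomisation number, which removes the ambiguity over screen failures.
4. If enrolment has begun (recruitment was due to end in September 2023), apply this with a fresh list for the remaining participants, and report the arrangement used until then.

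The cost is one reassigned task, one step moved later, and one contact with the list holder per randomisation. If enrolment is under way, there is also the work of making a new list and documenting the change.

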**Figure 2. fig2-02601060231190663:**
[figure not shown]
CONSORT flow diagram of the progress through the phases of the parallel randomized trial of three groups. CTRL: control group: EH: exercise in hypoxia; LCD: low carbohydrate diet.

### Interventions

Volunteers who meet the inclusion criteria will be asked to sign a written informed consent before enrolment in the trial, with the principal researcher. Participants will be randomized into control (CTRL), EH or interventions (EH + LCD) groups during 8 weeks. The CTRL group will perform an exercise protocol in normoxia with a control diet, and the other groups will perform the same exercise protocol in hypoxia (simulated altitude – nitrogen dilution method), following a control diet (EH) or an LCD (intervention group). Thus, we will compare whether EH group is more efficient than exercise in normoxia (CTRL group) and, if by including a LCD (EH + LCD group) the effects of EH group would be potentiated. We emphasize that during all test, physical exercise professionals, nutritionist, and doctors or nurses will be available.

### Dietary plan

An individualized dietary plan will be prescribed for each participant, using the software Dietbox®, version 7.0. The energy content of the dietary plan will meet 100% of the energy requirement for each participant, which will be estimated by multiplying the resting metabolic rate obtained by the Harris–Benedict equation, the most accurate at an individual level for older adults (Cioffi et al., 2021), and by a physical activity level, assessed using the International Physical Activity Questionnaire (IPAQ short form, last 7 days, elderly, self-administered format). Participants will be categorically rated into one of three levels of physical activity – low, moderate or high (Lee et al., 2011).

The energy distribution by macronutrients of the control diet of the CTRL and EH groups will be 60% from carbohydrates, 20% from protein and 20% from fat. The LCD will consist in 40% of energy from carbohydrates, 20% from protein, and 40% from fat. Both diets will be based emphasis on low-glycemic index foods and will limit saturated fat to 10% of energy, to reflect conventional dietary guidelines (Rodbard et al., 2007). We use the classification of diets as (a) very low-carbohydrate: less than 26% of the energy intake; (b) mild low-carbohydrate: 26%–45% of the energy intake; and (c) high carbohydrate ≥ 45% of the energy intake (Silverii et al., 2020). Thus, we will compare a mild LCD (EH + LCD group) to a high-carbohydrate diet (EH group). Compliance with the dietary plan will be assessed using weekly 24-h recalls. Participants will meet individually with a nutritionist twice within 8-week period to encourage adherence to the dietary plan.

### Exercise protocol

Both exercises in normoxia and in normobaric hypoxia at 3.000 m of simulated altitude, will take place 3 times per week, during period intervention of 8 weeks, in a hypoxic chamber at CMEP – Exercise Medical Center, Porto – Portugal. The chamber allows to control O_2_ (11%–20.97%), temperature (until 50 °C), humidity (until 80%) and altitude (until 8000 m). Altitude rating can be defined as (a) high altitude: 1.500–3.500 m; (b) very-high altitude: 3.500–5.500 m and (c) extreme altitude: Above 5.500 m, over sea level (Mathew and Sharma, 2022).

Exercise sessions will consist of 45 min of moderate aerobic exercise on a cycle ergometer and treadmill (Life Fitness, Illinois, USA) and 15 min of strength training, as recommended for this population (Bull et al., 2020). Moderate exercise intensity, which is considered an efficient strategy to improve cardiorespiratory and metabolic health in T2DM (Gildea et al., 2021), will be defined using 75% of the heart rate reserve, quantified in the pre-intervention cardiopulmonary exercise test (CPET). During each exercise session, heart rate and oxygen saturation will be constantly monitored using a finger pulse oximeter (Globus YM201, Milan, Italy). All exercise sessions will take place at the same time of day (± 2 h) and visits will be separated by at least 48 h of recovery.

